#### Secondary

To determine the effects of the intervention on: 1) changes in cIMT; endothelial function and arterial stiffness; 2) changes in arterial blood pressure (BP), blood lipids and lipoproteins; 3) changes in glomerular filtration rate (GFR) as assessed by plasma symmetric dimethylarginine (SDMA), creatinine and cystatin C levels; 4) changes in CVD risk markers: high-sensitivity C-reactive protein (hsCRP) and asymmetric dimethylarginine (ADMA); 5) incidence of retinopathy and subclinical changes in the retinal microvasculature; 6) quality of life, risk benefit, compliance and health economic assessment; 7) long-term outcomes with regard to incidence of DN and CVD.

### Study endpoints

The primary endpoint is defined as the area under the curve over time of log ACR per year, with standardization for gender, age and duration of diabetes.

The secondary endpoints are: 1) changes in cIMT, FMD, EndoPAT and PWV between baseline and the end of intervention period; 2) changes in arterial BP, lipids and other lipoproteins, CVD risk markers (hsCRP and ADMA), assessed every 6 months during the intervention period; 3) changes in measures of GFR (plasma SDMA, creatinine and cystatin C) assessed every 6 months during the intervention period; 4) changes in retinopathy scores and retinal microvascular structure (arteriolar or venular dilation, vascular fractal dimension, branching and tortuosity), assessed annually; 5) changes in quality of life and health economics.

### Methods/Design

#### Design of the RCT

The study is a multicenter randomized trial involving centers in the UK, Australia and Canada *(see additional file *1).

Subjects will be recruited from a pre-screened population of ~3,000 young people with T1D aged 11 to 16 years based on assessment of risk for future CVD and DN. Subjects deemed to be at high risk, based on their albumin excretion rate, will be randomized to a 2 × 2 factorial design contrasting the effects of ACEI, statins, or combination therapy to placebo over a three to four year treatment period. Minimization of variation between study arms in albumin excretion rate, gender, age, diabetes duration, HbA1c, total cholesterol and center location will be undertaken at randomization.

Analysis of the primary endpoint, change in albumin excretion, will be undertaken on an 'intention to treat' basis. Secondary analyses will be undertaken on the basis of 'as treated' allowing for variance in compliance and allowing for subjects who show substantial changes in HbA1c levels. Additional analyses will be undertaken to assess changes in the secondary objectives and to assess the overall effect of the intervention on quality of life and health economics.

#### Study population for the RCT

##### • Definition of high-risk subjects

Subjects with T1D within the age range 11-16 years are screened in the UK, Australia and Canada to determine the ACR in two sets of 3 early morning urines. The definition of a high-risk subject is based on previous data derived from the ORPS and Nephropathy Family Study (NFS) cohorts [41,76].

Preliminary data from the ORPS cohort (1,697 sets of urines from 479 subjects) indicated that the log standardized ACR based on the residuals from a regression model of log ACR adjusted for age, gender, age at diagnosis and duration of diabetes at 11-15 years was highly predictive of risk for the development of MA [44]. The average residual across visits provided a robust estimate of standardized ACR and a value above the cut-off point of 1.2 defines the high-risk upper tertile. A validation of the applicability of the ORPS ACR cut-off point and regression coefficients to another cohort was conducted in 690 subjects aged 11-15 years with ACR measures from two sets of 3 urines in the NFS. 27.5% had standardized ACR values in the top tertile; 93% of those selected using the ORPS coefficients and cut-off point would also have been selected with revised coefficients. This indicates good reproducibility, in a context where the mean HbA1c was 1% lower in the NFS when compared with the ORPS cohort.

During screening for AdDIT, two mean ACR measures, each based on three early morning samples, will have been provided by a subject. These will be averaged on the log ACR scale and the subject's average residual will be calculated using gender, age and duration and the coefficients from the ORPS linear regression model. If the subject's residual lies above log 1.2 the patient will lie in the upper tertile indicating high risk and eligibility for the trial.

*Inclusion criteria*

1) Age 11 to 16 years; 2) T1D diagnosed for more than 1 year or C-peptide negative; 3) Centralized assessment of ACR based on six early morning urines deemed to be in upper tertile for risk after adjustment for age, gender, age at diagnosis and duration of disease.

*Exclusion Criteria*

the presence of any of the following will prevent patient inclusion: 1) Non T1D, i.e. type 2 diabetes, insulin dependent diabetes related to monogenic disease, secondary diabetes; 2) ACR based on six early morning urines deemed to be at low risk for subsequent development of CVD or DN; 3) Pregnancy or unwillingness to comply with contraceptive advice and regular testing throughout trial; 4) Breast feeding; 5) Severe hyperlipidaemia and family history data to support diagnosis of familial hypercholesterolaemia; 6) Established hypertension unrelated to DN; 7) Prior exposure to the investigational products; 8) Unwillingness/inability to comply with the study protocol; 9) Other co-morbidities considered unsuitable by the investigator (excluding treated hypothyroidism and celiac disease); 10) Proliferative retinopathy.

##### • Sample size determination and power calculations

*Number of Subjects required*

The primary power calculation estimates that 400 subjects will need to be analyzed and we aim to recruit 500 to allow for dropouts and non-compliance.

*Power calculations based on the primary endpoint*

A 30% reduction in ACR is considered a worthwhile and plausible effect size to detect in this population and detection of a 25% reduction would be an advantage. With the 2 × 2 factorial design we plan for follow-up of 100 patients in each of the four arms: Placebo (P), ACEI (A), Statin (S), combination of ACEI and Statin (C). This sample size is informed by the ORPS cohort study (477 participants in the correct age range of recruitment with a mean of 3.5 observations over time) [13]. Within the tertile with the highest ACR standardized for gender, age and duration (defined as standardized ACR > 1.2), the standard deviation (SD) of standardized log to base 10 of ACR was 0.38 (mean 0.28) based on analyzing the final value alone, whereas the SD of the average standardized log ACR repeated over time, defined as area under curve per year, was 0.28 offering a reduction in detectable effect size from 30% to 25%. The primary endpoint is therefore defined as area under curve of log standardized ACR, with standardization for gender, age and duration of disease. The chosen sample size and endpoint provide 93% power to detect a 25% reduction in ACR attributable to the factorial main effect of ACEI (A and A+S arms [n = 200 total] versus P and S arms [n = 200 total]), and of Statin (S and S+A arms [n = 200 total] versus P and P+A [n = 200 total]). Additionally there is 82% power to detect a 30% reduction in ACR, in the following single-arm comparisons: A [n = 100] versus P [n = 100]; S [n = 100] versus P [n = 100]; and S+A [n = 100] versus P [n = 100].

*Power calculations for secondary endpoints*

For secondary outcomes, a 1% level of significance will be applied. For continuous outcomes, the sample size allows detection of small to moderate effect sizes; there will be 82% power in single arm comparisons to detect effect sizes of 0.5 SD between arms, and 93% power for factorial main effects of size 0.4 SD. For the secondary outcome cIMT, a pooled estimate across two studies of the SD of change from baseline is 0.044 [68]. There is 93% power to detect a 0.018 mm difference for ACEI and Statin factorial main effects, and 82% power to detect a 0.022 mm difference for single-arm comparisons.

For the secondary outcome FMD, an estimate across recent studies of the SD of change from baseline is 2.5. 180 subjects will give 80% power to detect a 1.5% difference in FMD between baseline and final assessment at a 5% level of significance.

For the secondary outcome PWV, an estimate across recent studies of the SD of change from baseline is 1.5. 200 subjects will give 80% power to detect a 0.85 m/sec difference in PWV between baseline and final assessment at a 5% level of significance.

For the secondary outcomes retinopathy and subclinical changes in the retinal microvasculature, the sample size will give greater than 90% power to detect a 25% difference in retinopathy prevalence and to detect a minimum of 3% change in retinal vascular parameters.

For binary outcomes, the sample size allows detection of moderate to large difference in proportion effect sizes, when the proportion is the mid-range of 0.2 to 0.8; so that there is 93% power to detect factorial main effects of a 50% relative reduction for proportions 0.4 versus 0.2, and the corresponding relative reduction detectable for the single-arm comparisons is 58%. For the secondary outcome of MA over the two measurements at age 18, the detectable reduction for factorial main effects is prohibitively large, 75%, due to a necessarily low prevalence in the treated arm, and therefore the more sensitive continuous ACR outcome will be the primary indicator of MA.

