##### • Sample size determination and power calculations

Based on a previous pediatric cohort of 45 patients with T1D with mean cIMT of 0.58 (SD 0.05), a sample size of 600 subjects at baseline (200 subjects evaluated per tertile of ACR) would allow mean cIMT in this population to be estimated precisely with 95% confidence interval of ± 0.004 mm and would provide 83% power to detect an unadjusted correlation of ≥ 0.12 between cIMT and ACR (α = 5%). This will allow sensitive detection of the association between ACR and cIMT after adjustment for potential confounders (such as age, gender, blood pressure, lipids, inflammation and HbA1c) using multiple linear regression.

For the analysis including data from baseline and at the end of the study, 300 subjects (100 high risk subjects from the RCT plus 100 low risk subjects from the middle and lower tertiles of ACR), the study will provide 80% power to detect correlation coefficients, such as between cIMT and ACR ≥ 0.16 (α = 5%). Assuming the same standard deviation of 0.044, analysis of the trend in cIMT across all three tertiles of ACR allows a range of ≥ 0.035 mm in mean cIMT to be detected across tertiles, and ≥ 0.022 mm between two tertiles. The analysis will include a regression model incorporating the 600 cIMT measures from subjects where cIMT was measured at both baseline and follow-up, to estimate the shape of progression of cIMT by gender and age over time and in relation to puberty and other potentially predictive characteristics.

For FMD, an estimate across recent studies of the SD of change from baseline is 2.5. 70 subjects will give >90% power to detect a 1% difference in FMD between baseline and final assessment at a 5% level of significance. For PWV, an estimate across recent studies of the SD of change from baseline is 1.5. 95 subjects will give 90% power to detect a 0.5 m/sec difference in PWV between baseline and final assessment at a 5% level of significance.

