### Statistical analysis

Continuous measures will be compared between groups using analysis of covariance, whereas binary outcomes will be compared using logistic regression. These models will involve adjustment for the randomization stratifiers, and for pre-randomization baseline outcomes to improve precision. The primary endpoint was correlated with baseline standardized ACR in the ORPS cohort (r = 0.3) indicating potential improvement in precision of estimated treatment effects. An initial test will be undertaken for exclusion of the factorial interaction of ACEI with Statin, with subsequent estimation of the factorial main effects of ACEI and Statin and single-arm comparisons. Subgroup analyses, for gender and for baseline standardized ACR (using a median split), will be undertaken by adding an interaction between the subgroup variable and factorial main effects followed by estimation within subgroups. Sensitivity analyses, such as for compliance and for raised HbA1c, will involve analysis using the same methods but applied omitting the relevant subjects or the relevant observations within subjects. For the HbA1c sensitivity analysis exclusions will be defined as those observations following the initial occurrence of a change in HbA1c from baseline in excess of 1%. An analysis restricted to the initial two measurements (first year) where short-term compliance is considered greater, will be performed and contrasted with the later period using within-patient analysis. Missing data will be primarily handled by excluding missing observations from analysis and secondly by multiple imputations [91] considering a contrast of both optimistic and pessimistic scenarios for treatment effects. Analyses will be on the primary basis of intention to treat, with as treated and per protocol as secondary. All tests will be two-tailed, and 5% and 1% significance levels will be used for primary and secondary outcomes respectively.

Formal interim analyses have not been incorporated into the design and analysis of the trial because the 3 to 4 year period of follow-up per subject is long relative to the recruitment period, and an interim analysis would detect early improvements without informing maintenance of any effect. The independent DMEC will determine how regularly to review efficacy and safety regularly, based on progressively longer mean treatment durations.

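### The primary power figures of 93% and 82% are too low for the stated SD, effects, group sizes and 5% level; the error is conservative

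*Protocol article*

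**What the plan says.** The Study 1 section *Sample size determination and power calculations* compares two ways of using the albumin/creatinine ratio (ACR) data from the earlier cohort. For a single final measurement, the SD of "standardized log to base 10 of ACR was 0.38 (mean 0.28) based on analyzing the final value alone". For repeated measurements, "the SD of the average standardized log ACR repeated over time, defined as area under curve per year, was 0.28". The article chooses the second as primary endpoint and says that this lowers the detectable reduction from 30% to 25%.

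It then states: "The chosen sample size and endpoint provide 93% power to detect a 25% reduction in ACR attributable to the factorial main effect of ACEI" (200 versus 200), with the same claim for the statin main effect. It adds 82% power for a 30% reduction in single-arm comparisons (100 versus 100). These are numbers analysed; the allowance for dropout and non-compliance is made by recruiting 500.

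For continuous secondary outcomes at a 1% level, the same section says "there will be 82% power in single arm comparisons to detect effect sizes of 0.5 SD between arms, and 93% power for factorial main effects"; the main-effect size it names there is 0.4 SD.

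The *Statistical analysis* section fixes the levels: "All tests will be two-tailed, and 5% and 1% significance levels will be used for primary and secondary outcomes respectively".

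On cIMT in Study 2, with 100 subjects per ACR tertile and SD 0.044 mm, the article says that the trend analysis "allows a range of ≥ 0.035 mm in mean cIMT to be detected across tertiles, and ≥ 0.022 mm between two tertiles".

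**The concern.** Every input to the primary power is printed, so the figures can be checked directly, and they do not follow. There is also a visible clash inside the sample size section. The 93% and 82% appear twice for the same group sizes: once for reductions that equal 0.446 and 0.553 SD at 5%, and once for 0.4 and 0.5 SD at 1%. A larger effect tested at a looser level must have more power, not the same power.

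These figures justify both the sample size and the choice of the area-under-curve endpoint. The article also relies on single-arm power if one arm closes or an interaction appears. Anyone weighing such a decision would start from numbers that do not describe the declared design.

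**Working it through.** **Inputs** (Study 1 sample size section, except the level and r, which are in *Statistical analysis*): SD 0.28 (log10) for the chosen endpoint; SD 0.38 for the final value alone; n = 200 or 100 per group; reductions of 25% and 30%; two-tailed 5% for primary and 1% for secondary outcomes; correlation with baseline r = 0.3.

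**Formula.** Difference δ = −log10(1 − reduction); standardised effect d = δ/SD; power ≈ Φ(d·√(n/2) − z), where z = 1.960 at 5% and 2.576 at 1%. Power figures below are from the noncentral t unless marked; the normal approximation agrees within one percentage point.

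**Step 1. The secondary figures reproduce.**
- 0.4 SD, 200 versus 200, 1%: 92.0% (normal approximation 92.3%), printed as 93%.
- 0.5 SD, 100 versus 100, 1%: 82.4%, printed as 82%.
- cIMT at 1%, SD 0.044: 93.3% for 0.018 mm and 82.4% for 0.022 mm, printed as 93% and 82%.

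**Step 2. The primary figures do not.**
- 25% reduction: δ = −log10(0.75) = 0.1249; d = 0.1249/0.28 = 0.446; 0.446 × √100 = 4.46; Φ(4.46 − 1.96) = Φ(2.50) = 99.4%. Printed: 93%.
- 30% reduction: δ = −log10(0.70) = 0.1549; d = 0.1549/0.28 = 0.553; 0.553 × √50 = 3.91; Φ(3.91 − 1.96) = Φ(1.95) = 97.4% (t: 97.3%). Printed: 82%.

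**Step 3. Other readings.**

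| SD | Level (two-sided) | 25%, 200 v 200 | 30%, 100 v 100 |
|---|---|---|---|
| 0.28 | 5% | 99.4% | 97.3% |
| 0.28 | 1% | 96.9% | 90.4% |
| 0.28·√(1 − 0.3²) = 0.267 | 5% | 99.7% | 98.3% |
| 0.38 | 5% | 90.7% | 81.8% |
| 0.38·√(1 − 0.3²) = 0.3625 | 5% | 93.0% | 85.2% |
| Printed | | 93% | 82% |

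No row gives both printed figures. The two rows that give one of them use the SD of the endpoint that the article did not choose. Shrinking the log effect by 20% for non-compliance (an assumption; the article states no such factor) gives 94.6% and 87.9% at SD 0.28 and 5% (normal approximation). Both figures would come out approximately with SD 0.31 at 1% (92.5% and 82.3%), or with SD 0.28 at a level of about 0.28%. The article states neither.

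**Step 4. Reductions that match the printed power at SD 0.28.** Required d = (z + z_power)/√(n/2); reduction = 1 − 10^(−0.28·d).
- 5%: d = 0.344 gives 19.9% (93% power, 200 v 200); d = 0.407 gives 23.1% (82%, 100 v 100).
- 1%: d = 0.405 gives 23.0%; d = 0.494 gives 27.3%.

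**Step 5. Study 2 side point.** A linear trend over three equal groups depends only on the two end groups, so its range is tested as a two-group comparison: (0.035/0.044) × √50 = 5.62. Power is Φ(5.62 − 2.576) = 99.9% at 1%, and higher at 5%. The 0.022 mm two-tertile figure has about 82% power at 1%, as in Step 1.

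**The case against.** The best defence is that the section was planned at 1% throughout and detectable reductions were rounded up to the next 5%. At SD 0.28, effects of 0.4 and 0.5 SD are reductions of 22.7% and 27.6%, which round up to 25% and 30%. Likewise, a 30% reduction at SD 0.38 rescales to 0.1549 × 0.28/0.38 = 0.114 log10, or 23.1%, at SD 0.28; the stated move from 30% to 25% is then that value rounded up. This is coherent and may well be how the figures arose. But the article does not say so, and its declared primary level is 5%. What stands is that the defect may be an undisclosed margin rather than a slip, and that the 25% in the endpoint comparison need not be a separate error.

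Three stronger readings might tempt a reader:
- **That the trial is underpowered.** The opposite holds on the stated inputs.
- **That it is oversized.** On the primary endpoint alone, 93% power for a 25% reduction would need about 120 per group. But the cIMT targets at 1% use the full 200 versus 200 and 100 versus 100, so the primary calculation alone does not make 400 excessive.
- **That a null result would exclude smaller effects than planned.** That will be read from the observed confidence interval, and it depends on the SD found in the trial, not on planned power.

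On Study 2, the trend sentence states neither level nor power, so no single replacement value can be derived.

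**Conclusion.** The primary power is understated: by about 6 points for the main effect (99.4% against 93%) and about 15 points for the single-arm comparison (97.3% against 82%). The printed figures also cannot be squared with the same figures given for smaller effects at 1%. The conclusion rests on the article's own SD of 0.28, its analysed group sizes, its declared 5% two-tailed level and a standard two-sample comparison. Baseline adjustment with r = 0.3 only widens the gap, and dropout is already covered by the difference between 500 and 400.

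The error is conservative and threatens neither validity nor recruitment. It should still be corrected, because these figures support the sample size and the choice of endpoint. The origin in a 1% level with rounding is plausible but remains an inference.

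The Study 2 range of 0.035 mm is a minor related point. With over 99% power at either level, it is not a usual detection limit.

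**What to change.** In the Study 1 sample size section, do one of the following:
- Restate at 5% with SD 0.28: about 99% power for a 25% reduction (200 versus 200) and 97% for 30% (100 versus 100); or 93% and 82% power for reductions of about 20% and 23%.
- If a 1% level, a larger SD or rounding was meant as a margin, state it and give figures that match. At 1% with SD 0.28 these are about 97% and 90% power, or 93% and 82% power for reductions of about 23% and 27%.

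In the Study 2 sample size section, state the test, level and power behind the 0.035 mm trend figure and correct it to match.

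The cost is wording only. The 500 recruited and 400 analysed stay as they are.

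### FMD and PWV power is stated at the 5% level although secondary outcomes are to be tested at 1%, and the comparison being powered is not named

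*Protocol article*

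**What the plan says.** The power section for Study 1 opens its treatment of secondary endpoints with a general rule: "For secondary outcomes, a 1% level of significance will be applied". The Statistical analysis section repeats it and fixes the sidedness: "All tests will be two-tailed, and 5% and 1% significance levels will be used for primary and secondary outcomes respectively". The Study endpoints section places both measures among the secondary endpoints, as "changes in cIMT, FMD, EndoPAT and PWV between baseline and the end of intervention period".

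The same power section then gives separate calculations for the two measures:

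- FMD: "For the secondary outcome FMD, an estimate across recent studies of the SD of change from baseline is 2.5", followed by "180 subjects will give 80% power to detect a 1.5% difference in FMD between baseline and final assessment at a 5% level of significance".
- PWV: "For the secondary outcome PWV, an estimate across recent studies of the SD of change from baseline is 1.5", followed by "200 subjects will give 80% power to detect a 0.85 m/sec difference in PWV between baseline and final assessment at a 5% level of significance".

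Nothing in the document exempts FMD or PWV from the 1% rule. Neither sentence says whether the comparison is one arm against another, a factorial main effect or a change within subjects, and neither gives a number per group.

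**The concern.** Two different significance levels are attached to the same tests. The neighbouring figures for continuous secondary outcomes in general, and for carotid intima-media thickness, are worked at 1%. A reader who compares them with the FMD and PWV figures is comparing powers at different levels without being told so.

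The unnamed contrast adds to the problem, because a difference between baseline and final assessment is not what a four-arm placebo-controlled trial tests. The Study 2 power section uses the same phrase for its own FMD and PWV figures, and there it does behave as a paired change.

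What is at stake is how a non-significant result would be read. Single-arm comparisons are planned analyses. The Statistical analysis section also relies on them as the safeguard if an ACE inhibitor by statin interaction appears, and says that power would remain adequate if an arm closed. For FMD and PWV, a reader relying on the stated 80% would give a null single-arm result more weight than it can bear at 1%.

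**Working it through.** **Inputs, all from the protocol article.** FMD: SD of change 2.5, difference 1.5, total 180. PWV: SD of change 1.5, difference 0.85, total 200. Tests are two-sided; the level is 5% in the two power sentences and 1% in the rule for secondary outcomes. There are four arms, planned at equal size for the trial as a whole. An equal four-way split of the 180 and the 200 is inferred, not stated.

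**Formula.** For a comparison of two groups of n, the standardised effect is d = difference / SD, and the non-centrality of the two-sample t-test is d × √(n/2) on 2n − 2 degrees of freedom.

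- FMD: d = 1.5 / 2.5 = 0.60
- PWV: d = 0.85 / 1.5 = 0.567

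**Step 1: reproduce the stated 80% at 5%.**

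| Reading | FMD power | PWV power |
|---|---|---|
| Arm v arm (180/4 = 45; 200/4 = 50 per arm) | 80.4% | 80.1% |
| Two halves (90 v 90; 100 v 100) | 97.9% | 97.9% |
| Paired change, all subjects | about 100% | about 100% |
| Paired change within one arm | 98% | 98% |

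Solving for 80% power at 5% gives 44.6 per arm for FMD and 49.9 for PWV. Rounded up and multiplied by four, these are 4 × 45 = 180 and 4 × 50 = 200, exactly the stated totals. Of the readings tried, only arm against arm fits.

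**Step 2: compare with the neighbouring figures.** At 1%, an effect of 0.5 SD with 100 v 100 gives 82.4% (stated 82%), and 0.4 SD with 200 v 200 gives 92.0% (stated 93%). At 5% these would be 94% and 98%. The general figures were therefore worked at 1%, and FMD and PWV depart from that.

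**Step 3: compare with the same phrase in Study 2.** As a paired test at 5%, FMD with 70 subjects, difference 1 and SD 2.5 gives 91% (stated: above 90%). PWV with 95 subjects, difference 0.5 and SD 1.5 gives 90% (stated 90%). So the phrase denotes a within-subject change in Study 2, but fits only a between-arm difference in Study 1.

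**Step 4: apply the 1% level with everything else unchanged.**

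| Contrast | n per group | Non-centrality | Power at 1% |
|---|---|---|---|
| FMD, arm v arm | 45 | 0.60 × √22.5 = 2.85 | 58.6% |
| PWV, arm v arm | 50 | 0.567 × √25 = 2.83 | 58.3% |
| FMD, main effect | 90 | 0.60 × √45 = 4.02 | 92.1% |
| PWV, main effect | 100 | 0.567 × √50 = 4.01 | 91.9% |

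The normal approximation gives 60.6% and 60.2% for the two arm v arm rows.

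**Step 5: what 80% arm v arm power at 1% would require.** With the numbers unchanged, the detectable differences are 1.84% for FMD and 1.04 m/sec for PWV. With the differences unchanged, the numbers are about 67 per arm for FMD (4 × 67 = 268) and about 75 per arm for PWV (4 × 75 = 300).

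**The case against.** The case on the other side has real force on four points.

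1. **The article never labels these figures single-arm.** That reading comes from dividing the totals by four. This stands: it must be reported as an inference, though it is the only reading tried that returns both stated totals.

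2. **The main effects are not short of power.** The analysis plan tests for interaction, then estimates main effects as well as single-arm comparisons. For main effects the same differences have about 92% power at 1%, which is above the stated 80%. A reader might infer that the trial is underpowered for FMD and PWV altogether. The document's own figures do not support that.

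3. **The planned analysis is not an unadjusted t-test.** The Statistical analysis section specifies analysis of covariance with adjustment for the baseline outcome, which can only help if the stated SD of change is right. The document gives no baseline-to-final correlation for FMD or PWV. Purely as an assumption, with equal variances at the two times, the residual variance is the change variance times (1 + r)/2. For r from 0.3 to 0.7, single-arm power at 1% is then about 81% down to 67% for both outcomes. So 58% is the like-for-like counterpart of the stated 80%, not a forecast for the adjusted analysis.

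4. **These are minor outcomes for the design.** FMD and PWV are measured only where centres have the facilities, they did not set the sample size, and the 5% level is openly stated in both sentences. This lowers the severity. It does not remove the conflict with the 1% rule.

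A reader might also want to extend the point to retinopathy, where "the sample size will give greater than 90% power to detect a 25% difference in retinopathy prevalence". The document does not support that. The section has already set 1% for secondary outcomes. Read as percentage points, the claim holds for main effects: 0.5 v 0.25 with 200 v 200 gives 99.6% at 1%. Low power appears only on a relative reading and at prevalences that the article does not give.

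**Conclusion.** The inconsistency is real and of moderate severity. The article applies a two-sided 1% level to secondary outcomes and states FMD and PWV power at 5%, without naming the contrast. The 80% is correct arithmetic at 5% for one arm against one arm, so this is an internal inconsistency and not a miscalculation.

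At the level the trial will use, the like-for-like power is about 58–59% for both outcomes, some 22 percentage points below the stated figure. This rests on three assumptions: an equal four-arm split of the 180 and the 200, the stated SDs of change, and an unadjusted comparison of change. Baseline adjustment may recover part of the loss, but how much cannot be determined from the document. Main effects keep about 92%. Neither the primary endpoint nor the overall sample size is affected.

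**What to change.** In the Study 1 power section, restate the FMD and PWV figures at 1%. Describe the contrast as the between-arm difference in change from baseline, and give the number per group. Either of these forms would do:

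- Differences of 1.5% FMD and 0.85 m/sec PWV have about 92% power as factorial main effects (90 v 90; 100 v 100) and about 58% as single-arm comparisons (45 v 45; 50 v 50), before baseline adjustment.
- The single-arm differences detectable with 80% power at 1% are about 1.84% FMD and 1.04 m/sec PWV.

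Alternatively, if 5% is what is intended for these two outcomes, state that exception in both the power section and the Statistical analysis section. The contrast still has to be named in that case.

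The cost is wording in the protocol and the matching text in the analysis plan. No endpoint, procedure or recruitment target changes, although under the 1% form the single-arm figures look less favourable. The choice of level should be recorded before unblinding, so that it cannot depend on the results.
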